### Outcome measures

The primary outcome is social functioning at 2 year follow-up. This will be measured using the Social Functioning Scale (SFS). The scale was developed in 1990, and has good reliability.^31 32^ It can demonstrate change over time^33–35^ and distinguishes different types of antipsychotic treatment.^33–36^ It also distinguishes between people in remission and those with an ongoing episode,^37^ people with long versus short duration of untreated psychosis,^38^ people who convert to psychosis versus those who do not in an ‘ultra-high risk’ cohort^34^ and between people who are employed versus unemployed.^31^ This scale was preferred to the Groningen Social Disability Scale (GSDS),^39^ which was used in the Dutch first-episode study, because of the GSDS is long, requires lengthy training and has a strong focus on relationships rather than functioning.

The main measure of the safety of the trial is severe relapse which is defined as admission to acute psychiatric inpatient treatment. This was selected because it is an objective criterion, can be precisely dated and can be obtained through patient records. Previous antipsychotic withdrawal studies have defined relapse in numerous different ways, with no consensus on defining criteria. Therefore, the current trial will also use an expert endpoint committee to assess the presence or absence of relapse based on blinded information from clinical case notes, based on predefined criteria and guidance.

Other outcome measures include: symptoms as measured by the Positive and Negative Syndrome Scale,^40^ subjective quality of life as measured by the Manchester Short Assessment of quality of life,^41^ adverse effects of antipsychotics measured by a modified version of the Glasgow Antipsychotic Side-effect Scale,^42^ body weight, sexual dysfunction as measured by the Arizona Sexual Experiences Scale,^43^ Work Productivity and Activity Impairment - General Health (WPAI) questionnaire,^44^ neuropsychological function (measured by a brief battery of tests designed for this trial, recovery as measured by the Questionnaire about the Process of Recovery,^45^ ICECAP-A (quality of life) and EQ-5D-5L (quality of life).

In addition, process data will be collected, including dose of antipsychotic medication (in haloperidol equivalents), patient satisfaction as measured by the Client Satisfaction Questionnaire^46^ and antipsychotic medication adherence as measured by Medication Adherence Rating Scale.^47^

Table 1 shows the time points at which each measure will be completed. All outcome measures are administered by research staff who have received standardised training. Data collected during assessments is stored in a secure online data management system provided by the Sponsor. Participant retention is promoted by sending correspondence and study newsletters to participants to facilitate engagement throughout the trial duration.

**Table 1 T1:** Time points at which different outcomes will be assessed

Visit number	Baseline	Follow-up				
	1.	2. Pilot trial 3 month data collection	3. 6 month follow-up	4. 12 month follow-up	5. 24 month follow-up	6. Qualitative evaluation
Informed consent	X					X
Eligibility determination	X					
Protocol assessments	A-I, L-O, Q, R	K	C-G, I-O, Q, R	C-O, Q, R	C-R	Indicative topic guide with sample of participants and psychiatrists
Randomisation	X					
IMP administration	X	X	X	X	X	
Adverse events review	X	X	X	X	X	
Medical notes review for prescribing information and fidelity to intervention protocols	X	X	X	X	X	
Concomitant medication review	X	X	X	X	X	

A, Demographic information (selected sections including weight and use of illicit drugs and alcohol); B, Diagnosis (established from clinical records); C, Social Functioning Scale (SFS); D, Positive and Negative Syndrome Scale (PANSS); E, Glasgow Antipsychotic Side-effect Scale (GASS); F, Client Satisfaction Questionnaire (CSQ-8); G, Manchester Short Assessment of quality of life (MANSA); H, Neuropsychological function tests; I, Medication Adherence Rating Scale (MARS-5); J, Relapse questionnaire; K, Serious Adverse Events; L, EQ-5D-5L; M, ICECAP-A; N, Client Service Receipt Inventory; O, Work Productivity and Activity Questionnaire; P, Schedule for economic data from patient records; Q, Questionnaire about the Process of Recovery (QPR); R, Arizona Sexual Experiences Scale (ASEX).

IMP, Investigational Medicinal Product.

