**Methods and analysis:**

This is a multicentre, randomised controlled trial involving people with schizophrenia and related disorders who have had more than one episode. Participants are randomised to have a clinically-supervised, gradual reduction of antipsychotic medication, leading to discontinuation when possible, or to continue with maintenance treatment. Blinded follow-up assessments are conducted at 6, 12 and 24 months and the primary outcome is social functioning, measured by the Social Functioning Scale at 24 months. A minimum of 134 evaluable participants provides 90% power to detect a five-point difference, and 206 to detect a four-point difference. Secondary outcomes include severe relapse (admission to hospital) and the study is also intended to detect a minimum 10% difference in severe relapse, which requires 402 participants, assuming a 15% loss to follow-up. Other secondary outcomes include all relapses, as identified by an independent and blinded endpoint committee, symptoms measured by the Positive and Negative Syndrome Scale, quality of life, adverse effects, self-rated recovery and neuropsychological measures. Enrolment started in 2016. The trial is scheduled to finish in June 2022.

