## Methods and analysis

### Study design

The trial consists of an open, parallel group randomised trial with concealed, individual randomisation. Randomisation is conducted through an independent, internet-based system linked with the database (https://www.sealedenvelope.com/randomisation/internet/) with 1:1 allocation. There are no replacements for participants who drop out or otherwise cannot comply with study procedures.

Participants and clinicians are aware of allocation, but outcome assessors are maintained blind to intervention arm as far as possible. This is achieved by nominating separate blinded and unblinded researchers at each site, and ensuring that blinded researchers are not exposed to discussions or written information that would reveal allocation. Following follow-up assessment blinded research staff record if they suspect they have guessed arm allocation.

The trial lasts for 2 years, with follow-up assessments conducted at 6, 12 and 24 months post randomisation. The trial design is presented in figure 1. Ethical approval includes the possibility of conducting a longer-term follow-up, and resources will be sought to support this at a later date.

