### Interventions

The antipsychotic reduction protocol was developed after consultation with professionals, academics and the trial’s RADAR Lived Experience Advisory Panel (LEAP). Both the antipsychotic reduction and maintenance protocols are administered by treating psychiatrists. For those participants randomised to the antipsychotic medication reduction arm, an individualised reduction schedule is devised by the research team for each participant based on clinical judgement and adjusted according to the participant’s initial antipsychotic regimen. The dose is reduced incrementally every 1 or 2 months, focusing on one drug at a time where participants are taking more than one antipsychotic. The rate of reduction varies according to baseline dose, with most schedules aiming for discontinuation within 12 months, but some lasting longer where baseline doses are high. Treating psychiatrists are asked to see the participants who have been randomised to antipsychotic reduction approximately every 2 months for the duration of the reduction, to adjust the medication regimen and monitor mental state. The participants are offered the option to discontinue antipsychotic medication completely if the reduction progresses well, or to reduce to a very low dose, defined as the equivalent of 2 mg of haloperidol a day or less, which is lower than the minimum recommended therapeutic dose for most antipsychotics. This is twice the dose that was defined as a ‘low dose’ in the Dutch first episode study,^24^ since some research suggests that doses of antipsychotic medication in people with first episodes should be around half those recommended for people with more established disorders.^29 30^ Guidance on the antipsychotic reduction strategy stresses the need for flexibility, and includes a suggested protocol for the treatment of adverse reactions to withdrawal or symptom exacerbation. Participants randomised to maintenance treatment are requested not to make major reductions in their dose of antipsychotic medication during the trial period. Increases in dose are permitted within the protocol, as are changes to a different antipsychotic agent at the same equivalent dose and minor dose reductions to address side effects.

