Participants are monitored by their care team according to usual practice. Patient records are scrutinised by members of the research team every 2 months to monitor the progress of the antipsychotic reduction and adherence to the maintenance protocol. Any deviations, such as participants allocated to reduction not starting or halting their reduction, are discussed with the treating clinician. All changes in antipsychotic doses and use of other medications is recorded throughout the study.

Other drug treatment and interventions such as psychological therapies may be used as indicated throughout the trial.

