### Risk reduction

The eligibility criteria are designed to exclude people with known high risks of causing harm to themselves or other people. In addition, the gradual nature of the antipsychotic reduction will enable detection and treatment of early signs of relapse. All participants will receive usual care and monitoring of their mental state and behaviour by their clinical team. Those randomised to antipsychotic reduction will have increased contact with a psychiatrist for the duration of the reduction, mirroring usual clinical practice with someone undergoing a significant reduction of medication.

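### The committee-judged all-relapse outcome is at risk of detection bias, because it rests on clinical case notes and only the reduction arm has scheduled extra psychiatrist reviews

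*Protocol article*

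**What the plan says.** The abstract of the protocol article lists the outcome: "Other secondary outcomes include all relapses, as identified by an independent and blinded endpoint committee". Under Outcome measures, the trial will "use an expert endpoint committee to assess the presence or absence of relapse based on blinded information from clinical case notes", applying criteria and guidance set in advance.

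Contact with psychiatrists differs by arm. Under Interventions: "Treating psychiatrists are asked to see the participants who have been randomised to antipsychotic reduction approximately every 2 months for the duration of the reduction". One stated purpose of these visits is to monitor mental state. Risk reduction describes the difference directly: "Those randomised to antipsychotic reduction will have increased contact with a psychiatrist for the duration of the reduction". For everyone, Interventions says: "Participants are monitored by their care team according to usual practice". Risk reduction likewise promises usual care and monitoring to all participants. No review schedule matching that of the reduction arm is given for the maintenance arm.

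On blinding, Study design says: "Participants and clinicians are aware of allocation, but outcome assessors are maintained blind to intervention arm as far as possible".

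Table 1 lists "J, Relapse questionnaire" and the PANSS (item D) within the assessments at 6, 12 and 24 months, for both arms. The article does not say that either is given to the committee.

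**The concern.** The committee cannot count a relapse that nobody wrote down. Admission leaves a record however often a patient is seen, but a milder exacerbation is recorded only if a clinician sees the patient, or hears of the problem, at the right time. Extra mental-state reviews in one arm give more such occasions there. They also fall in the period when withdrawal effects would be expected. The Introduction itself says that misidentified withdrawal effects may have inflated relapse rates in earlier trials.

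The stated aim is to learn whether gradual reduction can improve function while keeping worsening and relapse to a minimum. If part of an observed excess of non-admission relapse comes from closer observation, the strategy would look less safe than it is. The article names no analysis or data source that would let a reader judge how large that part is.

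**Working it through.** **Chain of reasoning, set against the text**

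1. Source: clinical case notes (Outcome measures).
2. Authors of the notes: clinicians aware of allocation (Study design).
3. Opportunity to record: usual monitoring in both arms, plus a psychiatrist review about every two months in the reduction arm only (Interventions; Risk reduction).
4. Duration: most schedules aim to finish within 12 months and some run longer, out of 24 months of follow-up (Interventions). The imbalance therefore covers roughly the first half for most participants who follow the schedule.
5. Safeguards stated: a blinded committee and predefined criteria. Both standardise the reading of the notes. Neither changes how often symptoms are seen and recorded.
6. The research team checks records every two months in both arms, but for progress of the reduction and adherence to maintenance. Checking records creates no new clinical observations.

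**Size**

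The article gives no event rate, margin or power for all relapses, so there is no figure to reproduce. What follows is an illustration on assumed inputs.

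- Assumed: equal true relapse risk p in both arms, from 20% to 40%.
- Assumed: probability that a true relapse reaches the notes, s_M (maintenance) and s_R (reduction), averaged over follow-up, with s_R higher by 5 to 20 percentage points.
- From the article: 402 randomised 1:1 and 15% attrition, so 402 × 0.85 = 341.7, about 171 per arm.

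Spurious excess = p × (s_R − s_M). Recorded risk ratio = s_R / s_M. The false-positive rate is the chance that a two-sided 5% normal test of two proportions rejects when true risks are equal.

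| s_M vs s_R | Risk ratio | Excess (points) at p = 20 / 30 / 40% | False-positive rate at p = 20 / 30 / 40% |
|---|---|---|---|
| 90% vs 95% | 1.06 | 1.0 / 1.5 / 2.0 | 5.7 / 6.1 / 6.7% |
| 80% vs 90% | 1.13 | 2.0 / 3.0 / 4.0 | 7.8 / 9.8 / 12.2% |
| 70% vs 90% | 1.29 | 4.0 / 6.0 / 8.0 | 17.3 / 25.6 / 35.6% |

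Example, p = 30% and 80% vs 90%: recorded risks are 0.30 × 0.80 = 0.24 and 0.30 × 0.90 = 0.27, an excess of 3 points. The standard error is √[(0.24 × 0.76 + 0.27 × 0.73)/171] = 0.047 and the shift is 0.03/0.047 = 0.64 standard errors. The rejection probability is about 9.8% instead of 5%.

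The gap is applied here to all relapses. If it held only during the reduction, and half of the relapses fell in that period (a further assumption), each excess would halve, and the range would be 0.5 to 4 points.

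**The case against.** The best defence has four parts.

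- **The committee's guidance is not shown.** It may already list further sources or deal with unequal contact, and the article does not rule out the relapse questionnaire as an input. This stands as a limit: one can say only that the questionnaire and PANSS are not named as committee sources. It does not remove the point, because the article itself fixes both the case-note source and the contact difference.
- **Both arms have their mental state monitored under usual care.** This is correct. Only the psychiatrist reviews are additional, and only while the reduction lasts.
- **Extra contact is part of the strategy and may avert relapses through early treatment.** This also stands. Relapses prevented are a real effect and could offset the recorded excess. A difference in recording is a measurement artefact, and the case-note outcome alone does not separate the two.
- **The main outcomes are protected.** The Social Functioning Scale does not depend on the notes, and admission was chosen as an objective criterion. This stands and limits the reach of the point.

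A reader might go further and infer that the relapse comparison is biased, by an amount to be set against the trial's 10% figure. The documents support neither step. No recording rates are given, so bias is a risk and its size is unknown. The 10% margin under Sample size calculation was set for hospital admission, and no margin is stated for all relapses.

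**Conclusion.** The concern holds as a risk of detection bias in one secondary outcome, the committee-judged all-relapse comparison. The likely direction of the recording artefact is towards more recorded relapse in the reduction arm, and committee blinding does not remove it. It bears mainly on non-admission relapse during the reduction period, little on severe relapse, and not on the primary outcome.

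The range of 1 to 8 percentage points rests wholly on assumed true relapse of 20-40% and an assumed recording gap of 5-20 points. It shows what is possible and does not estimate what will happen. This is a worthwhile, inexpensive improvement and no threat to the trial's main conclusions.

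**What to change.** Unless the committee guidance already does so:

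- Name the relapse questionnaire (item J) and blinded PANSS (item D) from 6, 12 and 24 months as committee sources in both arms, alongside the case-note extracts.
- Pre-specify a supportive comparison of relapse based only on these scheduled sources.
- Report the number of psychiatric contacts by arm.
- Record which contact first noted each event. Keep this hidden from the committee, since it could reveal allocation, and use it for description only.

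Do not add an analysis that excludes relapses recorded only at reduction reviews. It would remove events from one arm after randomisation, including some that another contact would have picked up, and so would build in a bias the other way. For the same reason, a difference between two such analyses would not by itself show a surveillance effect.

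The cost is a little more committee work, one extraction field and one supportive analysis, with no new assessments and no change to care. The supportive analysis will miss some relapses between visits and be less precise. The questionnaire is symmetric in timing, but participants know their allocation, so it is a check and not a reference standard.

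### Body weight is listed as an outcome, but Table 1 schedules it only at baseline; the two places need reconciling

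*Protocol article*

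**What the plan says.** The Outcome measures section of the protocol article includes weight as its own entry among the other outcome measures, between the side-effect scale and the sexual function scale: "body weight, sexual dysfunction as measured by the Arizona Sexual Experiences Scale".

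The text introducing the schedule then states: "Table 1 shows the time points at which each measure will be completed". The Study design section fixes the main visits, with "follow-up assessments conducted at 6, 12 and 24 months post randomisation". Table 1 adds a column headed "2. Pilot trial 3 month data collection".

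Table 1 lists assessments by letter, with a legend below. Weight is named once in that legend, as part of item A: "A, Demographic information (selected sections including weight and use of illicit drugs and alcohol". The only row that reviews clinical notes is described as "Medical notes review for prescribing information and fidelity to intervention protocols", which does not mention weight.

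**The concern.** An outcome in a randomised comparison needs at least one measurement after randomisation. A baseline weight describes the participants and can serve as a covariate, but it cannot carry a treatment effect. If the outcome list names weight and the schedule gives it only a baseline time point, the two parts of the article cannot both be followed.

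At stake is the between-arm comparison of weight. In the outcome list, weight is the only physical measurement of the body; the other entries are scales, questionnaires, cognitive tests or relapse events. The article expects recruitment to run until 2020 and the trial to finish in June 2022, so follow-up visits were still to come when it was written. A weight not taken by the research team at a visit cannot be taken afterwards.

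**Working it through.** The plan states no figure to reproduce here. The check is to expand the letter ranges in the Protocol assessments row of Table 1 and see where each listed outcome falls.

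**Step 1: expand the row.**

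| Column | Entry in Table 1 | Item A included? |
|---|---|---|
| Baseline | A-I, L-O, Q, R | yes |
| 3 months (pilot) | K | no |
| 6 months | C-G, I-O, Q, R | no |
| 12 months | C-O, Q, R | no |
| 24 months | C-R | no |

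The 6, 12 and 24 month entries all start at C, so A and B (diagnosis) are left out each time. Scheduled post-baseline weights: 0 + 0 + 0 + 0 = 0.

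**Step 2: compare with the rest of the outcome list.** These are the post-baseline time points for the measures listed alongside weight:

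| Measure | Item | Post-baseline time points |
|---|---|---|
| PANSS | D | 6, 12, 24 months |
| Side effects (GASS) | E | 6, 12, 24 months |
| MANSA | G | 6, 12, 24 months |
| Neuropsychological tests | H | 12, 24 months |
| EQ-5D-5L | L | 6, 12, 24 months |
| ICECAP-A | M | 6, 12, 24 months |
| Work productivity | O | 6, 12, 24 months |
| Process of recovery (QPR) | Q | 6, 12, 24 months |
| Sexual function (ASEX) | R | 6, 12, 24 months |
| Body weight | within A | none |

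Eight of the nine other measures have three post-baseline time points and the neuropsychological tests have two. Weight is the only one with none.

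**Step 3: look for weight elsewhere.** The other rows of Table 1 cover consent, eligibility, randomisation, IMP administration, adverse events, notes review for prescribing and fidelity, and concomitant medication. Item P is economic data from patient records. None names weight, and no other section of the article schedules a weight reading after baseline.

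**Step 4: read the wording of item A.** Its qualifier picks out selected sections of the demographic form, and the two it names, weight and substance use, can change over time. That is an odd description of a form completed once, in full, at baseline. It fits better with a form of which parts are repeated at follow-up. This is an inference from the wording; the article does not say that any part of item A is repeated.

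**The case against.** The strongest reply is that this is a slip in a table, not a flaw in the trial. The item A wording points that way. The article is a condensed account, sites work from the full protocol and its forms, and neither is shown here. Nothing in the article establishes that follow-up weight was left unscheduled or unrecorded. All of that stands, and it limits the conclusion to the printed schedule.

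It does not dispose of the point. Leaving a schedule to the full protocol would be no fault, but this article prints one, presents it as covering each measure, and contradicts its own outcome list. Nor does the table look damaged in extraction: the row has an entry for every visit, and the omission of A is the same throughout.

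Two further inferences are tempting, and the article does not support them:

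- A reader might see weight as central to the benefit that is weighed against relapse. The Introduction names diabetes, tardive dyskinesia and cardiovascular disease among physical complications, but not weight. The sample size section and the Discussion speak of side effects or adverse effects in general. Adverse effects are also still measured at every main follow-up visit by the side-effect and sexual function scales.
- A reader might extend the gap to illicit drug and alcohol use, which also sit in item A. Neither is listed as an outcome, so recording them once, as baseline characteristics, contradicts nothing.

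**Conclusion.** The inconsistency is certain on the face of the article: weight is a listed outcome, and the table said to time every measure gives it no time point after baseline. If Table 1 is the operative schedule and is followed as printed, weight has no post-baseline data and cannot be compared between arms.

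A reader might infer that follow-up weight has been lost for all of the up to 402 participants. The article does not support that. The loss depends on sites working from this table as printed, and the wording of item A makes an omission from the table a plausible explanation.

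The point is confined to one secondary outcome. The primary outcome (Social Functioning Scale at 24 months), the main safety measure (severe relapse) and the sample size do not depend on it. It still merits correction while visits remain: if the cause is a slip, the correction is trivial, and if it is not, a named outcome would go unmeasured.

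**What to change.** Reconcile the outcome list and Table 1. Either add the weight section of item A to the intended follow-up columns, or give weight its own letter at baseline and at those visits. The 6, 12 and 24 month visits are the natural candidates, because nearly all the other listed measures are taken there. Then check the full protocol and the data collection forms, and confirm that sites record weight at those visits.

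The cost is one table correction and, if weight is not already being taken, a brief reading at visits that are already planned. Nothing changes in the primary analysis, the relapse analysis or the sample size.
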